### Study procedures

60 participants will complete pre-test measures at baseline, after which half will be randomized to receive usual care, in addition to post-test measures following the completion of the intervention. Questionnaires will include demographic information, spiritual well-being (Functional Assessment of Chronic Illness Therapy – Spiritual Well-Being 12 Item Scale) [31], religiosity (Duke University Religion Index) [32], religious coping (Scale of Religious and Spiritual Coping) [33], quality of life (Functional Assessment of Cancer Therapy- General) [34], perception of care (Older Patient Assessment of Chronic Illness Care) [35], treatment burden (Treatment Burden Questionnaire) [36], distress (Distress Thermometer) [37], hope (Trait Hope Scale, State Hope Scale) [38,39], anxiety and depression (Hospital Anxiety and Depression Scale) [40]. For the purposes of this study, feasibility will serve as the primary outcome, with the others as secondary to explore preliminary impacts to guide subsequent larger studies.

### Acceptability and feasibility

Semi-structured acceptability interviews will be conducted with patients in the intervention arm two weeks after completing the SCAI program with the SC specialist. These interviews, conducted by study staff, will explore patients’ perceptions of the program, its impact, and any suggestions for improvements.

We aim for a 75% completion rate of study activities, defined as the proportion of enrolled participants who complete all components of the study protocol. This benchmark is consistent with retention rates of similar longitudinal clinical studies and reflects a realistic threshold to ensure the acceptability, feasibility, and relevance of our culturally tailored intervention to the target population [41–43].

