### Recruitment procedures

Recruitment will utilize previously successful procedures [26] in which the eligibility criteria (outlined above) are applied as screening parameters to identify patients through an electronicmedical record (EMR) review of diagnostic codes; a comprehensive list of patients meeting those criteria was generated and securely transmitted to the Principal Investigator via an encrypted electronic file. Eligible participants will receive an opt-out letter and a flyer by mail, detailing the study’s purpose and procedures. The letter will inform recipients that they will be contacted in two weeks unless they call the study phone number to opt out. After the two-week opt-out window, study staff will contact individuals who have not declined participation to provide details about the study. During this call, study staff will assess the individual’s interest in participating in the SC program. Participants expressing interest will be consented through Institutional Review Board (IRB)-approved verbal consent. Patients will receive $25 for each data collection activity they complete—baseline questionnaire, 12-week post-baseline follow-up questionnaire, and semi-structured interview (intervention group only)—for a maximum of $75 for completion of all study activities for intervention group participants and $50 for usual care group participants.

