### Randomization

Following the completion of the baseline interview, participants will be randomly assigned to receive either usual care from CGMHSA or the culturally-responsive SC intervention administered by a trained SC specialist (i.e., a board-certified chaplain) using stratified block randomization by sex and clinic type in REDCap. Since the intervention is administered as a feasibility pilot, the Principal Investigator and study staff will not be blinded. The participant flow is depicted in Fig 1.

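### The 75% completion benchmark for feasibility pools two arms with different task lists, so it can be met while all-component completion in the SCAI arm is well below 75%

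*Protocol article*

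**What the plan says.** Study procedures states that "feasibility will serve as the primary outcome, with the others as secondary". Acceptability and feasibility then gives the one numeric criterion at participant level, a "75% completion rate of study activities, defined as the proportion of enrolled participants who complete all components of the study protocol". The same section says that this figure "reflects a realistic threshold to ensure the acceptability, feasibility, and relevance of our culturally tailored intervention to the target population". The denominator is therefore everyone enrolled, in both arms, and the result is read as a statement about the intervention.

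The tasks differ by arm:

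- **Usual care:** baseline and 12-week questionnaires (Recruitment procedures).
- **SCAI:** the same two questionnaires, plus the session and one follow-up call (Spiritual Care and Assessment Intervention) and the semi-structured interview, which is for this arm only (Recruitment procedures; Acceptability and feasibility).

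The order matters too: "Following the completion of the baseline interview, participants will be randomly assigned". A randomized patient has already finished the baseline component.

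**The concern.** The quantity defined does not match the question it is meant to answer. Usual-care patients are never offered SCAI, so their completion says nothing about whether SCAI can be delivered. Yet they form half the denominator, and after randomization they have one task against four in the SCAI arm (visit, call, interview and 12-week questionnaire). If completion is higher where less is asked, the usual-care arm raises the pooled figure, and the target can be reached by a SCAI arm that falls clearly short of it.

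The stake is how the primary outcome is read. A pooled 75% would be taken as support for the feasibility of SCAI and carried into the larger studies that this pilot is meant to guide.

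**Working it through.** **Inputs from the protocol article.** Total 60, half to usual care, so 30 per arm (Study procedures). Benchmark 75% of all enrolled participants, all components (Acceptability and feasibility). The article gives no count, interval, power or expected completion rate for either arm, so there is no stated derivation to reproduce.

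**Assumptions.** All 60 are randomized 30:30, and patients complete independently. Usual-care completion is not given, so it is varied from 75% to 100%.

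**Step 1: the count.** 0.75 × 60 = 45 completers.

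**Step 2: the fewest SCAI completers that still meet it.** This is 45 minus the usual-care completers.

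| Usual-care completers | SCAI completers needed |
|---|---|
| 30/30 (100%) | 15/30 (50.0%) |
| 29/30 (96.7%) | 16/30 (53.3%) |
| 28/30 (93.3%) | 17/30 (56.7%) |
| 27/30 (90.0%) | 18/30 (60.0%) |
| 26/30 (86.7%) | 19/30 (63.3%) |
| 24/30 (80.0%) | 21/30 (70.0%) |

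**Step 3: how often the pooled target is met.** Let X ~ Binomial(30, p_SCAI) and Y ~ Binomial(30, p_UC), independent. The pooled probability is P(X + Y ≥ 45), by exact convolution. For comparison, the same all-component 75% applied to the SCAI arm needs 0.75 × 30 = 22.5, so at least 23, with probability P(X ≥ 23).

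| True SCAI all-component completion | Pooled, p_UC = 75% | 80% | 85% | 90% | 95% | 100% | SCAI arm alone, ≥ 23/30 |
|---|---|---|---|---|---|---|---|
| 50% | 0.024 | 0.056 | 0.116 | 0.218 | 0.372 | 0.572 | 0.003 |
| 55% | 0.061 | 0.125 | 0.230 | 0.382 | 0.572 | 0.769 | 0.012 |
| 60% | 0.131 | 0.238 | 0.388 | 0.571 | 0.755 | 0.903 | 0.044 |
| 65% | 0.242 | 0.392 | 0.570 | 0.746 | 0.887 | 0.970 | 0.124 |

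Both rules in this table count the same event, completion of every component.

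**Step 4: precision.** Exact (Clopper-Pearson) 95% intervals: 45/60 gives 62.1% to 85.3%; 23/30 gives 57.7% to 90.1%.

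**Step 5: what the counts do and do not measure.** A SCAI patient who attends the visit and takes the call but misses the interview or the 12-week questionnaire is a non-completer. All-component completion is therefore a lower bound on completion of the visit and call. For example, suppose (assumption) that 80% of those who finish visit and call also finish the rest. Then 60% all-component completion corresponds to 0.60 / 0.80 = 75% for visit and call, and P(X ≥ 23) at 75% is 0.514. If 75% do, it corresponds to 0.60 / 0.75 = 80%, and the probability is 0.761. The 0.044 in Step 3 therefore does not apply to a criterion based on visit and call alone.

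**The case against.** Five points can fairly be made for the plan.

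- **A reader might infer that SCAI could be declared feasible when barely half of its patients complete it, or when it was not deliverable.** The documents do not support that. The event counted is completion of all components, which is a floor on completion of SCAI itself (Step 5). The 50% figure also needs every control to complete. This objection stands.
- **The target is an aim, not a test.** The wording is "We aim for a 75% completion rate of study activities", with no hypothesis, error rate or go/no-go rule. That stands against any talk of a formal pass or declaration. It does not remove the mismatch, because the article itself calls the figure a benchmark and a threshold for the intervention.
- **High usual-care completion is assumed.** The article calls 75% consistent with retention in similar studies, which sits uneasily with near-perfect completion in controls. This is why a range is shown. At 75% usual-care completion, the pooled probability with a 60% SCAI arm is 0.13, still about three times 0.04 but far from 0.90.
- **Other evidence bears on feasibility.** There are interviews, specialist fidelity and uptake patterns. The 80% fidelity requirement applies to the specialists, however, and the interviews and uptake patterns carry no numeric criterion. The interviews also take place after SCAI has been completed, so they would not reach patients who never finished it.
- **Arm-level and component-level results may well be reported.** Nothing says that only the pooled figure will appear, and an article commonly leaves such detail to the full protocol or SAP. So it cannot be said that the plan hides where a shortfall arose. What remains is that the criterion the article does define is over the wrong group.

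The article's appeal to retention rates, which are not the same as completing every component, is a secondary matter. The cited sources are not available to check, and the text claims only consistency with them.

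**Conclusion.** The point holds in a limited form. The stated benchmark for the primary outcome is a pooled, all-component proportion used as a threshold for feasibility of the intervention, and it can be met with the SCAI arm well short of 75%. At 90% observed completion in controls, 60% in the SCAI arm is enough. With a true SCAI-arm rate of 60%, the pooled target is met with probability between 0.13 and 0.90 over the assumed control range, against 0.04 for the same event judged in the SCAI arm alone. The size depends on control completion, which the documents do not give, on 30 patients per arm and on independence between patients. The direction does not: whenever controls complete more often than SCAI patients, the pooled figure overstates completion in the SCAI arm. This should be fixed, but it does not undermine the trial: the target is aspirational, the trial is a 60-patient pilot, and the data needed are already being collected.

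**What to change.** Reword the criterion in Acceptability and feasibility:

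1. Apply the 75% benchmark to patients randomized to SCAI.
2. State which components count. For deliverability of the intervention, use the SCAI visit and follow-up call, and show the interview and the 12-week questionnaire separately.
3. Give 12-week questionnaire retention by arm, over all randomized patients.
4. Do not use the pooled figure as the criterion for feasibility of the intervention.

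The change is to wording only and needs no new data. The article reports 21 participants randomized as of October 2025 and preliminary analysis from July 2026, so on that timetable it can be made before results are examined. The cost is precision: at the benchmark, 23/30 carries an interval of 58% to 90%, against 62% to 85% for 45/60. Whether the new criterion is stricter depends on the components counted. On all components it is harder to meet than the pooled rule across the scenarios tabulated; on visit and call alone it may not be.

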### Spiritual well-being and religiosity

The Functional Assessment of Chronic Illness – Spiritual Well-Being 12 Item Scale (FACIT-SP-12) evaluates the spiritual well-being of individuals with cancer or other chronic illnesses [31]. With good internal reliability (ɑ = 0.81–0.88) and high internal consistency (ɑ = 0.96), the questionnaire is a valid and reliable measure of well-being across a variety of religious traditions and among ethnically diverse samples. The Scale of Religious and Spiritual Coping (RCOPE) assesses religious coping in regard to major life stressors and was initially tested among college students who had experienced a negative life event as well as hospitalized older adults [33]. The scale was found to have high internal consistency, incremental validity, and reliability. Meanwhile, the Duke University Religion Index (DUREL) measures religiosity across three major dimensions: intrinsic religiosity, organizational religious activity, and non-organizational religious activity. Previously administered to medical inpatients as well as older adults in large-scale epidemiologic studies, the DUREL has high test-retest reliability, high internal consistency (ɑ = 0.78–0.86), and high convergent validity with other measures of religious involvement [32].

### Quality of life, perception of care, and treatment burden

The Functional Assessment of Cancer Therapy- General (FACT-G) measures the quality of life of patients undergoing cancer treatment across the four domains of physical, social/family, emotional, and functional well-being. Although originally developed for individuals with cancer, it has been administered to populations with other chronic illnesses including heart disease, COPD, renal disease, and HIV/AIDS [34,44]. The instrument indicates high internal consistency (ɑ = 0.89) and test-retest reliability [34]; it was further found to be a valid and reliable scale when tested with older cancer patients [45].

The Older Patient Assessment of Chronic Illness Care (O-PACIC) is a 10-item instrument that assesses the perception of primary care from the perspective of older patients who have been recently discharged following hospitalization [35]. The O-PACIC shows good validity and internal consistency, and its short length entails that it can be feasibly administered to frail and chronically ill patients.

The Treatment Burden Questionnaire (TBQ) gauges treatment burden, or the ‘work’ of being a patient with chronic conditions and their impact on quality of life. Respondents are asked to rate the extent to which they consider particular aspects of their treatment to be a big problem or not a problem [36]. Originally developed in French, an English translation of the TBQ was administered to patients with chronic conditions across several countries including the US, United Kingdom, Canada, and Australia. Internal consistency (ɑ = 0.70–0.95) and test-retest reliability were further deemed to be acceptable**.**

### Distress, hope, and anxiety and depression

The Distress Thermometer instructs patients to rate their level of distress on a scale; scores range from 0 or “no distress” to 10 for “extreme distress.” Clinically relevant distress is signified by scores ≥ 3, and the scale is accompanied by an associated problem list of 34 issues that may have troubled respondents throughout the past week. Problems are arranged into categories: practical problems, emotional problems, spiritual/religious concerns, and physical problems [37]. Tested in cancer outpatients, the Distress Thermometer indicates a satisfactory level of accuracy and was found to be comparable to other distress measures.

The Trait Hope Scale measures the hope of a respondent according to Snyder’s cognitive model of hope; this model is based on a sense of successful agency or goal-directed determination as well as the perception of pathways for meeting goals [38]. The scale has been administered to college students as well as patients receiving psychological treatment, showing both high internal consistency (ɑ = 0.74–0.84) and good test-retest reliability. On the other hand, the State Hope Scale assesses the goal-directed thinking of individuals in the present moment and is responsive to the events of respondents’ lives [39]. Tested in samples of college students, the scale was found to be a valid and internally consistent measure of goal-directed determination and planning.

The Hospital Anxiety and Depression Scale (HADS) measures states of anxiety and depression for patients in a general medical clinic setting [46]. A score of 11 or higher indicates an abnormal case while scores in the range of 8–10 denote borderline cases. The HADS has been validated in elderly samples [46] and shows satisfactory internal consistency and test-retest reliability [47].

### Data analysis

#### Quantitative analysis.

Data from pre- and post-intervention questionnaires will be analyzed with SPSS; measures of effect size and bivariate tests of associations will be conducted to compare pre- and post-test measures. Due to the small sample size, broad patterns of responses will be examined.

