**Methods:**

A total of 60 African American patients who have chronic conditions and are aged 50 or older will be recruited for this study and randomly assigned to either the intervention (spiritual care program delivered by a board-certified chaplain) or the control group. All participants will complete a baseline interview that encompasses demographic information, religiosity, spiritual well-being, quality of life, and perception of care. Follow-up surveys will be conducted 12 weeks post-baseline, and participants assigned to the intervention group will also undergo a semi-structured acceptability and feasibility interview. Effect size measures and bivariate tests will be used to compare pre- and post-test outcomes while the interviews will be analyzed using constant comparative and thematic analysis.

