**Discussion:**

Study findings will assess the feasibility and effectiveness of a culturally-responsive spiritual care intervention for under-resourced African American patients with chronic illnesses. Furthermore, the provision of spiritual care may help patients clarify their healthcare values and decision making priorities.

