Recognizing the importance of these concerns, the 4^th^ Edition of the Clinical Practice Guidelines for Quality Palliative Care identifies spiritual, religious, and existential aspects of care as one of the key domains integral to delivering high-quality PC [18]. Spiritual care (SC) aims to recognize and respond to the needs of patients as they cope with trauma, illness, or grief [19]. Addressing spiritual needs is particularly important for addressing the structural inequalities related to PC and EOL care. AAs, for example, frequently experience poor communication regarding care options and goals of care [20], highlighting the necessity for culturally-responsive conversations and education regarding EOL decision making [6]. Ongoing spiritual support could help patients and family members be more accepting of PC and EOL care options [8].

This paper describes the study protocol for a culturally adapted SC intervention designed to support older AAs with heart failure (HF), chronic kidney disease (CKD), or chronic obstructive pulmonary disease (COPD) who are receiving care at a community safety net health service. This study aims to assess the acceptability, feasibility, and preliminary impact of the intervention on spiritual well-being, quality of life, and perception of care. HF, CKD, and COPD represent a substantial share of the chronic disease burden among AAs [21]; yet AAs living with these conditions remain underrepresented in clinical trials [22–24]. To address this gap, our study focuses on this population to generate data that can inform person-centered, culturally-responsive care. By centering the lived experiences and needs of older AAs with chronic illness, we aim to support the development of evidence-based practices that reduce disparities and improve outcomes in a group often overlooked in clinical research.

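### The stated quantitative analysis names only a pre-test versus post-test comparison and no SCAI versus usual care comparison, so natural change could be taken for intervention impact on the secondary outcomes

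*Protocol article*

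**What the plan says.** The Quantitative analysis section states that "measures of effect size and bivariate tests of associations will be conducted to compare pre- and post-test measures". It adds that, because the sample is small, only broad response patterns will be looked at. The Methods part of the abstract gives the same contrast: "Effect size measures and bivariate tests will be used to compare pre- and post-test outcomes". Neither sentence mentions study arm, and no other section names an arm comparison on a questionnaire outcome.

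The design is randomized and controlled. Under Study procedures, "60 participants will complete pre-test measures at baseline, after which half will be randomized to receive usual care". Under Randomization, assignment is made "using stratified block randomization by sex and clinic type in REDCap".

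The Introduction sets the purpose: "This study aims to assess the acceptability, feasibility, and preliminary impact of the intervention on spiritual well-being, quality of life, and perception of care". Study procedures ranks the outcomes: "feasibility will serve as the primary outcome, with the others as secondary to explore preliminary impacts to guide subsequent larger studies". The Discussion part of the abstract goes further: "Study findings will assess the feasibility and effectiveness of a culturally-responsive spiritual care intervention".

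**The concern.** The aim is about the effect of the intervention, but the only contrast named is about time. A pre-post difference in the SCAI arm is the sum of any SCAI effect and whatever would have changed over 12 weeks without it, such as illness course, ongoing clinic care and answering the same questionnaires twice. The usual-care arm is what allows the second part to be removed, and the stated analysis does not say it will be used for that.

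Testing each arm pre to post and comparing the two verdicts does not solve this, because significance in one arm and not in the other is not a test of the difference between arms. Pooling the arms does not solve it either: the pooled change contains the full natural change and only half of any SCAI effect.

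At stake are the effect sizes carried into the planning of a larger trial. If they are pre-post effect sizes, they do not estimate what that trial would be designed to detect. This is more than detail left to a fuller plan, because the article does name a contrast, twice, and it is not the one its aim calls for.

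**Working it through.** **Inputs from the protocol article.** Total sample 60 (abstract, Methods), half to usual care (Study procedures), so 30 per arm. Follow-up is at 12 weeks post-baseline (abstract, Methods). The completion target is 75% (Acceptability and feasibility), and 0.75 × 30 = 22.5, taken as 22. That target is for completing all study activities, so 22 per arm is only a scenario for 12-week questionnaire completers. The article gives no alpha, power, SD or effect size, so there is no figure of its own to reproduce.

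**Assumptions, not in the article.** No SCAI effect; a shift of 0.3 SD common to both arms; pre-post correlation r of 0.5 to 0.7; equal SDs at both times; two-sided 5% level.

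**Step 1: what each contrast estimates.** Write the common shift as s and the SCAI effect as δ, in SD units.
- SCAI-arm pre-post change: s + δ
- Pooled pre-post change: s + δ/2
- Between-arm difference: δ

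With s = 0.3 and δ = 0 the expected values are 0.3, 0.3 and 0. This holds for a purely descriptive effect size; no test is needed.

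**Step 2: paired test in the SCAI arm.** The SD of change is √(2(1 − r)): 1.00 at r = 0.5 and 0.775 at r = 0.7. The noncentrality is 0.3/√(2(1 − r)) × √n.

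| n per arm | r | Noncentrality | Paired test significant, SCAI arm | Pooled paired test significant |
|---|---|---|---|---|
| 22 | 0.5 | 1.41 | 27% | 49% |
| 22 | 0.7 | 1.82 | 41% | 71% |
| 30 | 0.5 | 1.64 | 36% | 63% |
| 30 | 0.7 | 2.12 | 54% | 84% |

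The pooled column uses the same formula with 2n patients.

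**Step 3: comparing two within-arm verdicts.** With p from Step 2, the chance that exactly one arm is significant is 2p(1 − p). At 22 per arm that is 2 × 0.269 × 0.731 = 39% (r = 0.5) and 2 × 0.411 × 0.589 = 48% (r = 0.7), with no true difference between arms.

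**Step 4: between-arm tests.** In a simulation of 4,000 trials per scenario, with no SCAI effect and common shifts of 0, 0.2, 0.3 and 0.5 SD, a between-arm t-test of change and a baseline-adjusted ANCOVA were each significant in about 4% to 5.6% of trials, whatever the shift. With no shift, the within-arm and pooled paired tests were also near 5%.

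**Step 5: gain from baseline adjustment.** The unadjusted between-arm 95% half-width at 12 weeks is 1.96 × √(2/22) = 0.59 SD with 22 per arm. At r = 0.6 (assumed), ANCOVA multiplies it by √(1 − 0.36) = 0.8, giving 0.47 SD. This is a gain in precision; the unadjusted comparison would also be valid.

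**The case against.** The strongest reply is that two sentences in a journal article are a summary. They do not say that an arm comparison is excluded, nor whether pre-post tests are run by arm or pooled. Tests of association could include arm against change or against 12-week score, and the usual-care arm completes both questionnaires, which fits such an analysis. This stands as far as it goes: a reader might infer that the trial will not compare arms, and the text does not support that. It supports only that the contrast named is pre versus post and that the arm contrast is not named. Hence natural change could, not would, be read as impact.

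Other stronger readings also fail:
- **Baseline data go unused.** They are the pre-test comparator. What is not stated is their use as a covariate in an arm comparison. That, like adjustment for the stratification factors, an article may leave to a fuller plan; the word bivariate in a summary does not rule it out.
- **Regression to the mean would produce a shift.** Eligibility uses no outcome score as an entry threshold, so the documents give no ground for a group-level shift of that kind.
- **The control arm contributes nothing.** In a feasibility trial it also informs randomization and completion of study activities.
- **The percentages are error rates of this plan.** The article states no significance rule for impact and no 0.3 SD shift, and it intends to look at broad patterns. The percentages illustrate the mechanism only.

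The emphasis on broad patterns does not remove the core point, since Step 1 applies to descriptive effect sizes too.

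**Conclusion.** The point holds in limited form. The contrast stated for the questionnaires, in both places where the analysis is described, does not match a randomized design whose stated purpose includes the impact of the intervention. Followed literally, it would give effect sizes that carry any natural 12-week change in full. Under a common shift of 0.3 SD and no SCAI effect, the expected pre-post change is 0.3 SD where the between-arm difference is zero. The size depends wholly on that assumed shift: if there is none, the pre-post tests have no excess of false positives.

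The affected outcomes are secondary and exploratory, so this should be fixed but does not threaten the trial's primary objective.

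**What to change.** Replace the sentence in Quantitative analysis, and its counterpart in the abstract, with text to this effect: for each continuous secondary outcome, the estimate of impact is the SCAI-minus-usual-care difference at 12 weeks, with participants analyzed as randomized, preferably by ANCOVA adjusted for the baseline score, sex and clinic type, reported with a standardized effect size and 95% CI; within-arm pre-post change is shown descriptively only.

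ANCOVA is preferred for precision. A between-arm comparison of change would also remove the common shift.

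The cost is wording plus about four degrees of freedom (one for baseline, one for sex, two for the three clinics). With 44 completers, 44 − 6 = 38 residual degrees of freedom remain after the intercept and arm. No new data are needed, and SPSS fits the model. The Results section places preliminary analysis in July 2026, so the text can be settled before outcome data are examined, which is worth doing because the investigators and study staff are not blinded.
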